This protocol addresses three gaps that, to our knowledge, have not previously been examined together in the BCI stroke rehabilitation literature. First, almost all existing BCI evidence is derived from chronic stroke survivors who have already plateaued after conventional rehabilitation, whereas the acute and early subacute inpatient phase, when neuroplasticity is theoretically greatest, remains largely untested. This phase also presents distinct patient selection challenges because reduced attention, fatigability, and medical instability are common early after stroke and may constrain who can engage with an attention-dependent motor imagery paradigm; this consideration directly informs our cognitive and tolerance-based eligibility criteria. Second, no existing study has evaluated the translation of BCI into routine ward practice through an implementation science lens despite well-recognized barriers relating to electrode set-up time, staffing, and device complexity. Third, no prior BCI rehabilitation study has reported a preliminary health economic evaluation, leaving decision-makers without cost-effectiveness evidence to guide adoption. In addition, the acute and severe stroke population has a particular need for, yet limited published safety data exist on, closed-loop BCI; systematic capture of adverse events such as fatigue, skin reactions, and seizure risk in this more vulnerable group is therefore a deliberate focus of this study.

The aims of this study protocol are to (1) establish the feasibility, usability, and safety of implementing BCI-based rehabilitation during the inpatient acute/early subacute stroke phase; (2) evaluate clinical efficacy outcomes with regards to motor impairment scales and quality of life measures; (3) characterize the electrophysiological correlates of motor recovery during this critical neuroplasticity window; and (4) conduct preliminary health economic evaluation.

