### 2.4. Sample Size

Based on comparable feasibility studies in BCI stroke rehabilitation literature and recommendations from our recent meta-analysis [24], a sample of 10 subjects will be sufficient for this feasibility study. Accounting for a 20% dropout rate (*n* = 2), the final proposed sample size is 12 participants. Recruitment will aim to stratify the sample by stroke type in an approximate ratio of 40% hemorrhagic (ICH) to 60% ischemic (infarct) stroke, consistent with local case-mix.

This sample size follows established guidance for pilot and feasibility trials, in which the objective is to estimate feasibility parameters and their variability rather than to test efficacy; widely cited recommendations propose approximately 12 participants for pilot studies [35,36], and a sample of 10–12 is adequate to estimate a feasibility proportion of about 80% (for example recruitment or adherence) with a 95% confidence interval half-width of roughly ±20%. A formal efficacy-based power calculation is therefore not appropriate for the present feasibility endpoints. Nonetheless, to inform the design of a future definitive trial, an indicative a priori power calculation was performed in G*Power (version 3.1). Anchoring conservatively on 6 points—the lower end of the FMA-UE minimal clinically important difference range established largely in chronic stroke (4–6 points)—acute-stroke-specific estimates are reportedly higher, approximately 7–10 points, but 6 points was retained as a conservative estimate and the pooled effect implied by our meta-analysis (mean change 5.23 points, standard error 0.70; approximate standard deviation 3.4 in the analyzed cohorts) [24]; a two-sided paired within-group comparison (α = 0.05, power = 0.80) would require approximately 6–8 participants to detect a change of the minimal clinically important difference magnitude, whereas a two-arm parallel comparison designed to detect a 4-point between-group difference at an assumed standard deviation of 6 (Cohen’s d ≈ 0.67) would require approximately 37–46 participants per arm. The variance and recruitment-rate estimates generated by the present feasibility study will be used to refine these calculations and to power the subsequent randomized controlled trial.

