**Interim Analysis:** An interim review will be conducted after enrollment of the first five patients. The interim analysis will evaluate eligibility verification (100% target), informed consent documentation (100% target), serious adverse event rate (0% target), adverse event rate related to training (≤17% target), and dropout rate (less than 20% during training phase). Continuation, modification, or termination of the study will be determined based on these interim metrics.

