We highlight the following limitations: Without a concurrent control group, any observed changes cannot be definitively attributed to the BCI intervention versus spontaneous recovery in the acute/subacute phase. This is a particularly important consideration in the 2–12-week window, when substantial spontaneous neurological recovery occurs and follows broadly predictable, proportional-recovery-type trajectories, making the separation of intervention-related gain from natural recovery intrinsically difficult in a single-arm design. To characterize and bound this confounder, we will (i) benchmark the observed FMA-UE and ARAT trajectories against the spontaneous-recovery estimates derived from the propensity-matched historical controls and from published early-recovery models, (ii) examine whether within-training electrophysiological change (ERD/ERS and decoding accuracy) tracks clinical change more closely than the passage of time alone would predict, and (iii) present sensitivity analyses that attribute conservative proportions of the observed gain to spontaneous recovery. These steps cannot substitute for a concurrent randomized control arm, which remains the definitive solution and is planned for the subsequent trial. The use of historical controls for economic evaluation introduces potential residual confounding. However, this study is intended as a pragmatic feasibility study that would in future support a larger study. The small sample size (*n* = 12) is appropriate for feasibility but limits precision, subgroup analysis, and generalizability, meaning that all findings are intended as hypothesis-generating to inform a future adequately powered trial. A specific consideration in this early phase is patient selection: motor imagery is attention-dependent, and the fatigue, reduced concentration, and medical instability that are common soon after stroke may limit who can engage with the paradigm. Determining which acute and early subacute patients can tolerate and reliably operate the BCI is therefore an explicit feasibility output of this study and will be used to refine eligibility criteria for a future definitive trial.

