For transparency, we set out each principal limitation together with the specific design improvement it motivates for a future adequately powered study: (1) the single-arm design will be replaced by a randomized, concurrently controlled trial; (2) reliance on historical controls, with its residual and temporal confounding, will be addressed through prospective concurrent recruitment and, for the economic analysis, contemporaneous comparators; (3) the small feasibility sample will be superseded by a sample size formally powered on the FMA-UE minimal clinically important difference and the variance estimates generated here; (4) the unequal rehabilitation dose will be resolved by a time-equated active or attention-controlled comparator; (5) the 24-week within-trial horizon will be extended by the long-term Markov extrapolation and by the additional 12-month clinical follow-up; (6) the incomplete separation of stroke etiologies will be addressed by pre-registering etiology- and severity-stratified subgroup hypotheses; and (7) the exploratory electrophysiological biomarker and action-observation predictors identified here will be advanced as pre-specified candidate predictors of response. Collectively, these refinements define a clear translational pathway from the present feasibility study to a definitive effectiveness and cost-effectiveness trial.

The findings from this study will have several important implications. Clinically, demonstration of feasibility and safety will support the integration of BCI technology into early stroke rehabilitation pathways. The identification of MI-EEG correlates with clinical efficacy measures will inform early treatment-related plasticity effects. A comprehensive economic evaluation will inform preliminary justification of the additional device and set-up costs and efforts required. The preliminary economic data will help healthcare administrators and policymakers understand the potential value proposition of BCI technology in stroke rehabilitation to inform resource allocation decisions.

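### Aim 1 and the Discussion speak of establishing or demonstrating safety, but 12 participants can only describe it: even no serious training-related event leaves a per-participant risk of up to 22–26%

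*Protocol article*

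**What the plan says.** Aim 1, at the end of 1. Background, is to "establish the feasibility, usability, and safety of implementing BCI-based rehabilitation during the inpatient acute/early subacute stroke phase". Section 4 (Discussion), in its paragraph on implications, states: "Clinically, demonstration of feasibility and safety will support the integration of BCI technology into early stroke rehabilitation pathways". The closing paragraph of section 4 again speaks of safety being established in the present study, there as a step towards tele-rehabilitation.

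Other places are more cautious. The limitations paragraph of section 4 says that, because of the small sample, "all findings are intended as hypothesis-generating to inform a future adequately powered trial". The Abstract calls the evidence on safety preliminary.

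Section 2.4 says that "a sample of 10 subjects will be sufficient for this feasibility study" and, after a dropout allowance, that "the final proposed sample size is 12 participants". Its precision argument concerns a feasibility proportion near 80%, with recruitment and adherence as the examples.

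The safety criterion in section 2.5 is training-related adverse events per delivered session of at most 17%. It counts headache, pain, skin changes, visual symptoms, mental fatigue and seizures together. A serious adverse event target of zero appears only in section 3.12, for the interim review after five patients.

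**The concern.** A result that only generates hypotheses cannot also be a demonstration of safety that supports integration into care. The sentences in 1. Background and in the implications paragraph of section 4 carry no limit of their own. In that implications paragraph the economic data are called preliminary, while safety is not.

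This matters because 1. Background says that published safety data in this population are limited, and names capture of seizure risk among the events of deliberate interest. If the trial sees no serious related event, the present wording allows the result to be described as safety shown, with no indication of how large a risk remains compatible with the data.

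**Working it through.** **Inputs.** Total sample 12, from 10 plus a 20% dropout allowance, and the 95% confidence level (section 2.4); up to 15 sessions each (section 2.6); safety benchmark 17% per delivered session (section 2.5); interim review after 5 patients (section 3.12).

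**The plan's own figures.** 10 × 1.20 = 12, as stated. For a proportion of 80%, the simple 95% half-width is 1.96 × √(0.8 × 0.2 / 12) = 22.6 points at n = 12 and 24.8 points at n = 10. The Wilson half-width for 10 of 12 is 20.1 points. The stated half-width of about 20 points is therefore reached only at the favourable end. It says nothing about a rare event in any case.

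**Best possible result for serious events.** With no event in n participants, the exact upper limit is 1 − α^(1/n), where α = 0.05 (one-sided) or 0.025 (two-sided).

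- n = 12, one-sided: 1 − 0.05^(1/12) = 22.1%.
- n = 12, two-sided: 1 − 0.025^(1/12) = 26.5%.
- Other methods at n = 12: Wilson 24.3%; rule of three 3/12 = 25%.
- Interim, n = 5, one-sided: 1 − 0.05^(1/5) = 45.1%.

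**How often a real risk would go unseen.** The chance of no event in 12 is (1 − p)^12.

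- p = 5%: 0.95^12 = 54%.
- p = 10%: 0.90^12 = 28%.
- p = 20%: 0.80^12 = 6.9%.

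**Size needed for a tighter limit, given no events (one-sided).** An upper limit of 10% needs ln 0.05 / ln 0.90 = 28.4, so 29 participants. A limit of 5% needs ln 0.05 / ln 0.95 = 58.4, so 59.

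**Does the per-session benchmark help?** The maximum is 12 × 15 = 180 sessions, and 0.17 × 180 = 30.6, so up to 30 training-related events would meet it. The criterion does not separate a seizure from fatigue, so meeting it does not bound serious risk.

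**Does a per-session denominator help?** No event in 180 sessions gives 1 − 0.05^(1/180) ≈ 1.7% per session. Treating sessions as independent, the same limit over a 15-session course is 1 − (0.05^(1/180))^15 = 1 − 0.05^(1/12) = 22.1%. The smaller figure is a change of unit and adds no information about the risk to a participant who completes the course.

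**The case against.** The best defence is that the limits are already there. The limitations paragraph covers all findings, and safety is one of them. The Abstract says preliminary. The paragraph just before the implications lists seven limitations and places a definitive trial next. The verb in the pathway sentence is *support*, which is weaker than *justify*. All of this stands, and it makes the point a minor one. It does not remove the mismatch, because the object of that verb is integration into care pathways and not progression to the next trial.

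Four stronger readings are tempting, and the document does not support them.

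- A reader might infer that the plan claims serious events or seizures are rare per participant, or that a clean result would trigger routine use. It states neither. Its criterion is per delivered session, its stated focus is systematic capture of events, and no decision rule links zero events to adoption.
- A reader might apply the limit to 10 completers. Sections 3.13 and 2.4 give no ground for that: events are recorded at every session, so those who drop out also contribute.
- A reader might fault the absence of a stated interval for safety. An article may leave this to the full protocol or analysis plan, so it is not a defect here.
- A reader might conclude that 12 is too few. For the feasibility aims that does not follow; any pilot of this size has the same limit on rare harms.

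**Conclusion.** The point holds as a minor inconsistency of wording with a consequence for reporting. Aim 1 and two sentences in section 4 promise more on safety than the limitations paragraph and the Abstract allow, and more than 12 participants can give. With no serious related event, the compatible per-participant risk extends to 22% (one-sided) or 26% (two-sided).

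These figures assume that all 12 are treated and counted, that participants are independent, and that 95% confidence applies, as in section 2.4. At one-sided 90% confidence the limit would be 17.5%, which does not alter the conclusion.

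**What to change.** 1. In Aim 1 (1. Background), and in the implications and closing paragraphs of section 4, replace establishing or demonstrating safety with describing safety and tolerability and detecting early signals.
2. Confine the stated clinical implication to informing progression to the planned randomised trial, in line with the limitations paragraph.
3. Report the number of participants with any serious related event, including seizure, out of all treated participants, with its exact upper 95% limit, also when the count is zero.

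This costs three edits and one exact interval. Design, sample size, data collection and the feasibility benchmarks stay as they are. The only downside is a less favourable stated implication.

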## Figures and Tables

**Figure 1 jcm-15-05692-f001:**
[figure not shown]
The distribution of time since stroke at the initiation of BCI-based rehabilitation against baseline upper limb impairment, drawn from our published individual patient data meta-analysis of existing BCI stroke studies [24]. Each point represents one patient; the horizontal axis shows time since stroke in months on a logarithmic scale, and the point color denotes the change in Fugl–Meyer Assessment Upper Extremity score following BCI-based therapy. The shaded band marks the first three months after stroke. The overwhelming majority of patients in existing studies were treated in the chronic phase, with only 8.8% commencing BCI-based rehabilitation within the first three months. This illustrates the paucity of evidence for the acute and early subacute window that the present study seeks to address.

**Figure 2 jcm-15-05692-f002:**
[figure not shown]
A schematic of a single recoveriX motor imagery brain–computer interface trial. Each trial comprises a 2 s baseline period, an auditory cue signaling trial initiation, a 1 s delay, and a visual cue (an animated arrow) presented with a concurrent auditory instruction indicating whether to imagine left or right finger extension, followed by 5 s of motor imagery with real-time feedback. Motor imagery is decoded every 200 ms; upon detection, functional electrical stimulation is delivered to the forearm finger extensor muscles while an on-screen avatar displays the corresponding hand movement, providing synchronized multimodal sensory feedback.

**Table 1 jcm-15-05692-t001:** Outcome measures and assessment instruments.

Outcome Measure	Score Range	Description
Motor Impairment and Upper Limb Function		
Fugl–Meyer Assessment—Upper Extremity (FMA-UE)	0–66	Standardized, highly inter-reliable tool for the assessment of motor impairment in stroke-related hemiplegia; higher scores indicate less impairment [34]
Action Research Arm Test (ARAT)	0–57	Assessment of upper limb function including grasp, grip, pinch, and gross motor movements

**Healthcare Utilization Costs (Both Groups)**	
Inpatient rehabilitation	Length of stay, ward type (Class B2/C subsidized wards as reference case), average daily bed cost, total OT/PT sessions
Outpatient services	Rehabilitation clinic visits, community therapy sessions (post-discharge)
Readmissions	Any stroke-related or rehabilitation-related hospital readmissions within 24 weeks

**Table 3 jcm-15-05692-t003:** RE-AIM framework assessment domains and variables.

Domain	Variables to Be Collected
Reach	Percentage excluded by eligibility criteria; proportion of eligible patients who participate; characteristics of participants versus non-participants
Effectiveness	Primary outcome measures (FMA-UE, ARAT); quality of life outcomes; adverse events; subgroup analyses; cost-effectiveness metrics
Adoption	Setting exclusion rates; patient disposition; staff participation rates; characteristics of participating versus non-participating staff
Implementation	Protocol adherence and fidelity rates; adaptations made during study; time and resource costs; consistency across staff and settings
Maintenance	Long-term primary outcomes (6+ months); sustained subgroup effects; organizational adoption sustainability

## Data Availability

The datasets generated during the current study will be available from the corresponding author on reasonable request.
